### Outcome Measures

#### Primary Outcomes

The primary outcomes are levels of depressive symptoms measured with the PHQ-9 [31] and levels of functioning measured with the WHODAS 2.0 [32] at posttreatment (8 weeks after baseline).

The PHQ-9 is a well-known 9-item instrument measuring presence and severity of depression [31]. As a severity measure, the PHQ-9 score may range from 0 to 27, since each of the 9 items can be scored from 0 (not at all) to 3 (nearly every day). The PHQ-9 has been validated in the Lebanese population with a cut-off score of 10 or above indicating moderate depression [33]. The PHQ-9 is now one of the main outcome measures worldwide that is used in research on psychological interventions and has been chosen as one of the core metrics for research on psychological interventions that should be included in all studies on psychological interventions for depression and distress funded by the Wellcome Trust, the National Institute of Mental Health, and other major funders [34].

The WHODAS 2.0 is a generic assessment instrument assessing health and disability [32]. It is used across all diseases, including mental, neurological, and substance use disorders, and in many global regions. It is simple to administer, is applicable across cultures, and can be used in all adult populations. WHODAS 2.0 covers 6 domains (cognition, mobility, self-care, getting along, life activities, participation). It assesses difficulties people have across these domains during the last 30 days. Difficulties are scored as none, mild, moderate, severe, or extreme.

#### Secondary Outcomes

Secondary outcomes include levels of subjective well-being (WHO-5) [35], levels of anxiety symptoms (Generalized Anxiety Disorder-7 [GAD-7]) [36], and levels of PTSD symptoms (PTSD Checklist for DSM-5 [PCL-5]) [37]. In addition, subjective problems are assessed using the Psychological Outcomes Profile Instrument (PSYCHLOPS) [38]. Satisfaction will be assessed using the 3-item version of the Client Satisfaction Questionnaire (CSQ) [39], and service utilization will be measured with an adapted version of the Client Service Receipt Inventory (CSRI) [40]. Please see Figure 2 for an overview of the different measures at different time points.

**Figure 2 figure2:**
[figure not shown]
Schedule of enrollment, interventions, and assessments for Step-by-Step (SPIRIT figure). CSQ: Client Satisfaction Questionnaire 3; GAD: Generalized Anxiety Disorder; PCL-5: PTSD Checklist for DSM-5; PHQ: Patient Health Questionnaire; PSYCHLOPS: Psychological Outcomes Profile Instrument; SRI: Service Receipt Inventory; WHO: World Health Organization; WHODAS: World Health Organization Disability Assessment Scale.

The WHO-5 Well-Being Index is a 5-item questionnaire measuring current psychological well-being and quality of life, rather than psychopathology [35]. Scores range from 0 to 25. The scale has demonstrated sensitivity to change in well-being and is available in multiple languages.

The GAD-7 is a 7-item self-report questionnaire for generalized anxiety disorder widely used in primary and specialist care as an indicator of anxiety symptoms [36]. It consists of Likert scale questions including items on nervousness, anxiety, restlessness, and fear. It is being included in this study as a means to investigate whether the intervention, which includes a stress reduction exercise and cognitive coping strategies, may reduce comorbid symptoms of anxiety. The GAD-7 has been validated in the Lebanese population [33].

PTSD symptoms during the past week will be measured using the abbreviated 8-item version of the PCL-5 [37]. Items are rated on a 5-point scale from 1 to 5 and add up to a total severity score of 30. The previous short version of the PCL (PCL-6) [41] that was based on the diagnostic criteria of DSM-IV has shown good psychometric properties and has been tested in diverse cultural settings, including Lebanon [42].

PSYCHLOPS [17] is a person-centered outcome measure consisting of 4 questions across 3 domains: problems (2 questions), functioning (1 question), and well-being (1 question). Participants are asked to indicate self-identified problems. Responses are scored on an ordinal 6-point scale producing a maximum score of 20 (5 points per question). The pre- and postintervention versions of PSYCHLOPS consist of the same 4 questions but the posttherapy version adds an overall evaluation question (determining self-rated outcome ranging from “much better” to “much worse”). PSYCHLOPS has been validated in primary care populations across several countries [20,21]. It is currently used in WHO studies in Pakistan, Kenya, and Uganda.

The CSQ [39] is an easily scored and administered 8-item measure that is designed to measure client satisfaction with mental health services. It includes an additional free response field as well as the 8 questions that are scored on a Likert scale. To decrease questionnaire burden, this study used the 3-item version of the CSQ [43].

The CSRI was developed for the collection of data on service utilization and related characteristics of people with mental disorders, as the basis for calculating the costs of care for mental health cost-effectiveness research [40]. The CSRI was adapted for online use within a large European Union–funded program, the STRENGTHS program [21], further adapted by the team for use in Lebanon and pilot-tested in the feasibility RCT.

During the course of the intervention, the PHQ-4 [44] will be used to monitor depressive symptoms on a weekly basis regardless of progress in the sessions. The 4-item version has shown good psychometric properties, and the Arabic version was validated among displaced Syrian people in Germany [44,45].

Data on sociodemographic information (sex, age, education, marital status, and work status) will be collected through questions A1-A5 of the 12-item self-report version of the WHODAS 2.0. In addition, users will be asked where they heard about the study.

### Data Management

Most data will be collected electronically in the app, and all electronic data will be stored on password-protected computers. The data collected through computers or devices will be downloaded from the platform and migrated into a data analysis software program. Hardcopies of data from the study (for example, from qualitative interviews and supervision notes) will be safely stored in locked cabinets. No personal data will be used in publications or presentations. The accuracy of data storage and output will be monitored bi-weekly by an external person.

Because of the nature of this innovative intervention and the data being collected online, considerable emphasis has been given to privacy and security of client data. Programming of the iOS and Android apps and web versions is being managed by Freie Universität Berlin. The intervention software and all procedures involving the software will be developed in compliance with the European Union General Data Protection Regulation.

### Data Analyses Plan

#### Statistical Analyses

For the 2 RCTs, both ITT analysis (including all randomized participants) and completers’ analyses (per protocol) will be carried out. First, the mean differences between the 2 treatment arms at baseline, postintervention, and 3-month follow-up will be determined. Then, the treatment effect will be estimated based on ITT analysis using regression estimation models with the principal predictor being treatment assignment status. Missing outcome observations for participants will be imputed using multiple imputation exploiting prescores and a set of prespecified background characteristics (gender, age, education, and severity of symptoms). Given that there are 2 primary outcomes of interest, we will impute using multivariate normal regression using an iterative Markov Chain Monte Carlo method based on initial treatment assignment. The aforementioned prespecified covariates and baseline measurement of primary endpoint will be added to the baseline model for improved precision. Potential bias concerns as a result of nonrandom missing outcome observations will be addressed by estimating Lee bounds. Then, 95% confidence intervals will be constructed, both for the regression-generated point estimates and Lee bounds [46] interval estimates. To further tighten confidence interval bounds in the context of differential and potentially nonrandom attrition between treatment arms, Random Forest Lee Bounds will be estimated (using the approach in Cornelisz et al [47]).

These treatment effect analyses will be performed for both primary outcome measures, PHQ-9 and WHODAS 2.0. Concerns of multiple testing error will be addressed by maintaining an experiment-wise type I error of 5%. In order to address potential heterogeneity, treatment effects will be estimated for subgroups (eg, based on prescores). Finally, average treatment effects on the treated will be estimated treatment and corresponding measures of clinically meaningful change, and numbers needed to treat (using the approach in Furukuwa et al [48]) will be explored.

In addition, the same analyses will be carried out for analyzing clinical outcomes measured at each assessment time: anxiety (GAD-7), wellbeing (WHO5), posttraumatic stress reactions (PCL-5, 8-item version), and self-identified symptoms (PSYCHLOPS).

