The intervention was first developed as an internet intervention and then developed into an iOS and Android app [21] that can be used mostly offline on mobile devices and into a web app that can be accessed via a web browser. These RCTs are testing Step-by-Step as a guided self-help intervention in which Step-by-Step is supported by trained nonspecialist research assistants (called “e-helpers”), who have weekly phone-based or message-based contact lasting approximately 15 minutes with users to provide support and guidance. E-helpers have an undergraduate degree in psychology or social work and work under the regular supervision of trained mental health practitioners. They will receive a 4.5-day training in the research protocols and the intervention itself, including how to guide users in implementing the techniques learned in the intervention and how to use the online system. They are supported in this by a manual and clear session-by-session outlines for the support contacts. Knowledge and therapeutic skills covered in the e-helper training include working with people with depression and other mental health problems, identifying and dealing with crisis situations, and responding to adverse events (AEs). E-helpers need to pass a competency test to be involved in the RCTs. During the trials, fidelity checks will be conducted to ensure adherence to the guidance protocol using a treatment fidelity checklist. The supervisor and the study coordinator will supervise up to 5% of the responsive support contacts through listening in to calls and reviewing messages.

Weekly clinical supervision will be provided to e-helpers by a clinical supervisor from MoPH with a good understanding of the Step-by-Step intervention and research project. Clinical supervision will ensure fidelity of the guidance provided and involves discussion of difficulties encountered in supporting the users of the intervention, as well as self-care for e-helpers. In addition, weekly supervision on research processes will be provided by the local study coordinator.

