#### Enhanced Care as Usual (ECAU)

ECAU will consist of basic psychoeducation and referral to evidence-based care. If randomized into the ECAU condition, users will first receive basic psychoeducation on depression via the hybrid app. The text for the psychoeducational messages is taken from the first session of Step-by-Step to make sure the information provided is identical. After receiving the psychoeducation, ECAU users will receive a list of selected primary health care facilities with staff trained in the mhGAP where they can seek evidence-based care as usual consisting of assessment and pharmacological or psychosocial management of mental health conditions according to mhGAP [8].

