### Randomization

Upon completion of the baseline assessment, participants will be randomized to either the intervention or ECAU, using a 1:1 allocation ratio. The randomization is handled by an algorithm for permuted block randomization that is built into the app and not accessible to the research team. The algorithm generates a random sequence of blocks with varying length. In each block, the number of seats for both groups is even, and the order is fully random.

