### Sample Size Calculation

A recent meta-analysis of depression treatments in low- and middle-income countries has been conducted with 32 RCTs, looking at different intervention types, formats (eg, guided self-help, group therapy), and comparators (eg, waitlist, treatment as usual) [25]. An effect size of 0.73 (Hedges *g*) was found for symptoms of depression. Moreover, a recent meta-analysis of internet-based and mobile-based interventions for the treatment of depression in high-income countries, including 19 RCTs, showed an effect size of 0.90 (Hedges *g*) when comparing these treatments with the waitlist condition [26,27]. Despite these relatively high effect sizes reported in literature, the power calculation for these RCTs was completed for a more conservative (but still clinically significant) effect size of Cohen *d* = 0.5.

Assuming one primary outcome, power of 90%, and α of .05, the 2 RCTs need 85 participants in each of the 2 arms, in order to be able to detect a moderate effect size of 0.5. For the 2 primary outcomes considered, this yields a complete power (ie, the probability to detect statistically significant effects of at least 0.5 on both outcomes, given that both effects truly exist) ranging from 81% (independence between outcomes) to 90% (perfect correlation between outcomes). For individual power (ie, the probability of detecting an effect of 0.5 or larger for a particular outcome, given that the specific effect truly exists), applying a Bonferroni multiple testing procedure to control the family-wise error rate at or below an α of .05 yields an individual power of 84% [28]. We note that Bonferroni is overly conservative in the case of dependency between outcomes, such that the true family-wise error rate is likely to be somewhat below 5% [28].

In our feasibility RCT, we found a dropout rate of 70%, which is consistent with other e-mental health studies [29,30]. Accounting for a dropout rate of 70% [(2*85)/(1-0.70)=568], 568 displaced Syrian people and 568 other people residing in Lebanon will thus be recruited for the trials such that 85 are estimated to complete the intervention (complete 4 of 5 sessions) in the intervention arms of each trial.

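### E-helper guidance exists in one arm only, and neither the sample size nor the described model allows for correlation of outcomes within e-helper

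*Protocol article*

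**What the plan says.** The section on the Step-by-Step intervention describes guided self-help supported by trained non-specialist e-helpers, "who have weekly phone-based or message-based contact lasting approximately 15 minutes with users to provide support and guidance". The control arm differs: "ECAU will consist of basic psychoeducation and referral to evidence-based care", delivered through the app with a list of facilities. Under Procedures, e-helpers also contact control participants, but about assessments that are due. Individuals are randomised: "participants will be randomized to either the intervention or ECAU, using a 1:1 allocation ratio".

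The Sample Size Calculation takes a "more conservative (but still clinically significant) effect size of Cohen" *d* = 0.5 and states: "Assuming one primary outcome, power of 90%, and α of .05, the 2 RCTs need 85 participants in each of the 2 arms". A Bonferroni correction for two outcomes "yields an individual power of 84" percent. Recruitment is then inflated for dropout only: "Accounting for a dropout rate of 70% [(2*85)/(1-0.70)=568" per trial.

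Under Statistical Analyses, the effect is estimated "using regression estimation models with the principal predictor being treatment assignment status". The section goes on to name the covariates, the imputation variables, a multivariate normal imputation method run by assignment, and two forms of Lee bounds. It also promises an experiment-wise type I error of 5%. The e-helper appears in neither the outcome model nor the imputation model.

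**The concern.** Users guided by the same e-helper share that person's skill and style, so their outcomes may be correlated. Controls have no such shared source. This is a partially nested design: individuals are randomised, but one arm is clustered by provider after randomisation. A regression that treats every participant as independent then omits the between-helper part of the variance in the intervention arm.

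What is at stake is the precision claimed for both primary outcomes in both trials. The article aims at scale-up and release to other settings, where other e-helpers would give the guidance. For that purpose, variation between e-helpers belongs in the standard error.

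**Working it through.** **Inputs from the article:** two-group comparison, *d* = 0.5, α = 0.05 (two-sided reproduces the plan; sidedness is not stated), power 90%, 85 per arm, 70% dropout, 568 per trial (284 per arm), 1:1 allocation.

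**Assumptions (not in the article):** number of e-helpers per trial *k* = 5 to 20, ICC = 0.01 to 0.05, equal caseloads, one e-helper per user, equal total variance in the arms, no gain from covariates.

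**Step 1: the plan's own figures.**
- *n* per arm = 2(1.960 + 1.282)² / 0.5² = 84.1, rounded up to 85.
- Power at α = 0.025 with 85 per arm: standard error √(2/85) = 0.153; 0.5/0.153 = 3.26; 3.26 − 2.24 = 1.02, giving 84.6% (84.0% with the *t* distribution).
- Both outcomes significant if independent: 0.90² = 81%.
- Dropout: 85/0.30 = 283.3, rounded up to 284 per arm, 568 per trial.

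All agree with the article at a design effect of 1, so the sample size carries no allowance for e-helper clustering.

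**Step 2: partially nested variance.** With *m* = *n*/*k* users per e-helper, the design effect in the intervention arm is DE = 1 + (*m* − 1)·ICC. The ratio of true to unadjusted standard error is √[(DE + 1)/2]. The actual level of a nominal 5% test is 2[1 − Φ(1.96/ratio)].

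Example with *k* = 5, *n* = 85, ICC = 0.05: *m* = 17; DE = 1 + 16 × 0.05 = 1.80; ratio = √(2.80/2) = 1.183; 1.96/1.183 = 1.657, so the level is 9.8%. Power is Φ(3.26/1.183 − 1.96) = Φ(0.795) = 78.7%.

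**Step 3: the range with 85 analysed per arm.**

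| *k* | ICC | DE | SE ratio | Level of nominal 5% test | Power, α 0.05 | Power, α 0.025 |
|---|---|---|---|---|---|---|
| 20 | 0.01 | 1.03 | 1.008 | 5.2% | 89.9% | 83.9% |
| 8 | 0.01 | 1.10 | 1.024 | 5.6% | 89.0% | 82.7% |
| 5 | 0.01 | 1.16 | 1.039 | 5.9% | 88.0% | 81.5% |
| 20 | 0.05 | 1.16 | 1.040 | 5.9% | 88.0% | 81.4% |
| 8 | 0.05 | 1.48 | 1.114 | 7.8% | 83.3% | 75.3% |
| 5 | 0.05 | 1.80 | 1.183 | 9.8% | 78.7% | 69.6% |

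At ICC = 0 the ratio is 1 and nothing changes. These are normal approximations. With small-sample degrees of freedom, the last row's 78.7% becomes about 70%.

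**Step 4: upper case, all 284 per arm contributing.** Over the same 5 to 20 e-helpers, the ratio is 1.03–1.13 at ICC 0.01 (level 5.8–8.3%) and 1.15–1.55 at ICC 0.05 (level 8.9–20.5%). Power at α = 0.05 stays at or above 97% by the normal approximation, or about 90% in the worst cell with small-sample degrees of freedom. With this many analysed, the problem is interval width rather than power.

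**The case against.** A reader might infer that the regression treats all outcomes as independent, that there are few e-helpers, and that the standard errors are therefore too small. The article supports none of these as flat statements.

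- **Independence.** It is explicit only through the sample size arithmetic. The analysis section names no variance estimator, this is a condensed article, and a separate analysis plan might add an adjustment. This stands. Still, the section is detailed on covariates and imputation and includes no e-helper term, so following it as written gives unadjusted standard errors.
- **Number and stability of e-helpers.** The number, the caseload and whether a user keeps one e-helper are not given. This stands, and is why only a range can be shown.
- **Size of the ICC.** The app carries the therapeutic content. Support is brief and standardised by a manual, session outlines, a competency test, fidelity checks and supervision. These features should keep the ICC low, but they do not make it zero.
- **Type I error.** If neither the program nor its e-helpers affect anyone, e-helper contact creates no correlation and the ordinary test keeps its level. Inflation needs a zero average effect with real e-helper differences around it. This stands. The more general consequence is intervals that are too narrow.
- **The 284-per-arm figures.** With 70% dropout planned, many of the 284 would have little e-helper exposure, and imputed values add no information about e-helpers. This stands, so 85 per arm is the safer guide.
- **Control contact.** E-helpers also contact controls, but the contact described concerns assessments, so treating controls as unclustered is reasonable.

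**Conclusion.** The point holds in conditional form. Guidance by e-helpers is confined to the intervention arm, and neither the sample size nor the described regression and imputation allows for it. If the e-helper ICC is above zero, unadjusted standard errors and 95% intervals for both primary outcomes would be too narrow.

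Under the assumptions above and 85 analysed per arm, the effect runs from negligible (ratio 1.01, 20 e-helpers, ICC 0.01) to material (ratio 1.18, 5 e-helpers, ICC 0.05). In that last case the stated 90% power would be about 79%, and the stated 84% about 70%. The documents do not show that the standard errors will in fact be wrong, or by how much. They show only that the plan as described would neither reveal nor correct it.

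**What to change.** - Attach an e-helper identifier to each intervention participant. The Qualitative Evaluation section refers to e-helper records of client contacts, so it should be recoverable. If an e-helper served both trials, keep the same identifier.
- Prespecify for both primary outcomes, at least as a sensitivity analysis, a partially nested model: a random e-helper effect in the intervention arm only, controls unclustered, separate residual variances by arm, and small-sample degrees of freedom.
- Impute separately by arm with the e-helper included, or show a complete-case version alongside. Imputing without the e-helper would pull the estimated ICC towards zero.
- Report the number of e-helpers, the caseloads and the ICC with its interval.
- State in the sample size section that the 90% and 84% power figures assume no e-helper clustering. Data collection is complete, so the sample size itself cannot change.

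The cost is somewhat wider intervals, extra work on the imputation model, and an imprecise ICC if e-helpers are few. If the ICC proves close to zero, the conclusions will barely move.

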#### Health Economic Analysis

The health economic evaluation will be conducted from the perspective of the health care system to determine the difference in costs over the difference in outcomes in the intervention arm as compared to the ECAU condition.

Costs include intervention cost (eg, costs for hosting and maintaining the intervention, costs for e-helpers) plus health care costs (eg, participants’ service use as assessed with the adapted CSRI). In addition, we will attempt to compute costs stemming from productivity losses owing to absenteeism and presenteeism (work cut back). Costs will be expressed in international dollars for the reference year 2019.

In the health economic evaluation, the central outcome will be treatment response defined as a pre-post symptom reduction of at least 50% on the PHQ with PHQ posttest scores below the cut-off of 10, thus indicating a clinically significant reduction in depressive symptoms. Treatment response will be defined in a similar way for WHODAS 2.0.

Costs, C, and effects, E, will combined in the incremental cost-effectiveness ratio (ICER) defined as (C_1_- C_0_)/(E_1_ – E_0_), where subscripts 1 and 0 refer to the intervention and ECAU conditions, respectively. The ICER can be interpreted as the additional cost per treatment responder.

Stochastic uncertainty in the ICER will be captured as a scatter of simulated ICERs over the ICER plane using 2500 bootstraps. For decision-making purposes, an ICER acceptability curve will be plotted indicating the likelihood that the intervention can be regarded as more cost-effective than the ECAU condition given a range of willingness-to-pay ceilings. Finally, sensitivity analyses will be directed at uncertainty in the main cost-drivers. The Consolidated Health Economic Evaluation Reporting Standards (CHEERS) guideline [49] will be followed when reporting the cost-effectiveness analysis.

